### Translational objective (secondary 1)

To assess the MSB Program’s efficacy versus Control to enhance adoption of twice-daily fluoridated toothpaste use and consumption of a low cariogenic diet. We hypothesize that the MSB Program will increase adoption of twice-daily fluoridated toothpaste use and consumption of a low cariogenic diet.

### Explanatory objective (secondary 2)

To assess causal pathways (i.e., mediators and moderators) through which the MSB Program influences twice-daily fluoridated toothpaste use and consumption of a low cariogenic diet. We hypothesize that the MSB Program will influence motivation, the ability to act on motivation, and support to maintain oral hygiene and dietary behaviors which may be conditioned by demographic, social, and contextual factors.

### Subjects and setting

This RCT will recruit 858 boys and girls aged 24–71 months with visually evident ECC from Columbia University Irving Medical Center (CUIMC) pediatric medical and dental clinics. They will be randomly assigned equally to Intervention and Control Groups along with their parent or primary caregiver (i.e., the person with legal responsibility for housing and safety, hereinafter referred to as parent). If parents present with more than one age-eligible child, the youngest child will be enrolled.

### Eligibility

Eligible parents must be 18 years or older, have a cell phone with texting capabilities, and plan to remain in the New York City metropolitan area for 12 months after enrollment (Fig. 1). Although open to all racial/ethnic groups, the demographic makeup of the targeted catchment area increases the likelihood that the majority will self-identify as Hispanic. Eligible children must be 24–71 months of age, have a minimum of 12 teeth present, have no disqualifying medical condition (that would limit oral dietary intake, at-home oral hygiene practices, or receipt of oral examinations), and have apparent ECC or Severe ECC (S-ECC) as defined for research purposes [33] on visual examination with light and dental mirror. Suspected ECC/S-ECC at recruitment will be later confirmed upon dental examination by a pediatric dentist trained in the International Caries Detection and Assessment System (ICDAS) if the child demonstrates the presence of one or more decayed (*d*) cavitated or non-cavitated lesions with ICDAS Category 2 or greater, missing (*m*) due to caries on history, or filled (*f)* tooth surfaces in any primary tooth or meets criteria for S-ECC. The ICDAS defines Category 2 as distinct visual change in enamel; Category 3 as localized enamel breakdown due to caries with no visible dentin; Category 4 as underlying dark shadow from dentin; Category 5 as distinct cavity with visible dentin; and Category 6 as extensive distinct cavity with visible dentin [34].

### Recruitment

Parent–child dyads will be recruited in the waiting rooms of one pediatric dental and four pediatric medical clinics of the Columbia University Irving Medical Center (CUIMC) in the Washington Heights neighborhood of New York City. Upon presentation, receptionists will give parents a printed statement substantiating their provider’s endorsement of the study and allowance of waiting room recruitment. Recruitment posters in both English and Spanish will be posted in waiting areas and examination rooms. Recruiters, who are bilingual community health workers (CHWs) will approach parents of young children to explain the study and invite participation. Community Health Workers will obtain informed consent for subsequent eligibility screening, collect parent’s primary and alternative contact information, schedule the screening appointment at the Columbia Community Partnership for Health (CCPH) research and community-engagement facility, and provide the parent with a pre-loaded MetroCard (value $5.50) to cover the cost, if any, of transportation to and from the CCPH. Parents will receive an appointment confirmation call or text message the day before the scheduled CCPH eligibility-screening visit.

Additionally, snowball recruitment will be employed by asking parents to solicit others with age-appropriate children for examination at the enrollment facility. If parents express interest in involving other parents, they will be given a separate recruitment flyer and business card for their friend’s use in contacting an MSB Program CHW.

### Enrollment

At the CCPH screening visit, all parents will be given a gift card valued at $20.00, provided a written report of screening findings, and offered a written referral for routine follow-up dental care along with a printed list of area dentists who treat young children. Parents of children confirmed to have ECC will be invited to participate in the study, asked to provide written informed consent, and informed that they will be randomized to a Control or Intervention Group. Parents who enroll in the study will complete an interview with a CHW, which includes administration of the pre-intervention survey instrument. Their children will receive a visual oral examination with tooth surface-specific charting of caries experience at this baseline visit (T1). Parents will confirm agreement to attend a follow up visit at 12 months (T2) when they will again participate in a CHW interview and survey and their children will have a second study-specific dental examination and charting. Enrolled parents who meet these requirements will be given an additional $30.00 participation incentive. Randomization will be stratified by age (24-48 and 49-71 months) and recruitment site, with approximately equal numbers in each Group using a biased-coin design facilitated by computerized randomization software. Oral examinations will be performed in a consistent manner by one of two study dental examiners blinded to Group assignment.

### Participant incentives

In addition to the MetroCard (value $5.50) to facilitate transit to the CCPH, $20 gift card for presentation at CCPH, and $30 gift card for enrolling in the study, parents who complete the study by participating in T2 examination, interview, and survey will be given gift cards valued at $100 (i.e., up to $155.50 total value).

### Intervention group

At the CCPH visit—in addition to the child’s dental examination, parent’s interview, and completion of the intake survey—Intervention Group parent–child dyads will participate in an observed video-recorded tooth brushing demonstration, receive toothbrushes and toothpaste for the entire family, be provided study-specific educational materials, and receive their CHW’s business card for contact as desired. Based on observation of tooth brushing behaviors, the CHW will offer instruction that promotes skills, helps parents overcome barriers, and bolsters parental self-efficacy. The family will be provided with sufficient toothbrushes and over-the-counter fluoridated toothpaste for the entire family’s use at T1 and replenished quarterly for 12 months (until T2). Printed educational materials will describe the caries process, promote a low cariogenic diet (based on recommended frequency, duration, content, and timing of cariogenic foods and drink consumption), and detail elements of therapeutic tooth brushing (twice daily with appropriate amount of fluoridated toothpaste, by parents, for at least 1 min).

At T1, Intervention Group parents will also engage with a CHW in the first round of the MSB Program. Using the MSB App, positioned to facilitate parents’ engagement, CHWs will involve parents in a conversation that fulfills the first four components of the MSB Program:Education: on caries pathogenesis using videos and models;Caries risk assessment: completion—in any order that feels appropriate to the conversation—of a caries risk assessment that includes considerations of feeding practices, fluoride use, family caries history, beliefs and attitudes regarding caries, and a modified 24-h dietary recall using a unique widget that derives an algorithm-driven dietary cariogenicity score;Goal setting: parent selection of a specific tailored oral health behavioral goal related to an identified high-risk behavior; andAction planning: development of a written action plan that specifies who in the family’s circle will do what, with whom, where, when and how to achieve the stated goal.

The fifth Program component—Follow up and Facilitation—will be achieved over six months through at least three CHW-parent interactions and automated delivery of standardized study-specific text messages. Of the three interactions, at least one will be an in-home visit (or, if necessary, a virtual in-home visit) that will include a timed tooth brushing observation during which CHWs will provide additional guidance and instruction if necessary. Two additional interactions may be conducted by telephone or reciprocal text messaging. Interactions will focus on review and reinforcement of the family’s goal and the family’s progress toward fulfilling their self-defined action plan. Up to four additional interactions with parents may be provided by CHWs if needed to address pressing parental concerns related to food, housing, income, employment, or immigration insecurities by making referrals to appropriate community, social service, and legal aid programs. All interactions will be recorded to analyze possible impacts on study outcomes. The standardized text messages are comprised of 4 rounds of 12–13 messages each over the course of the 6-month intervention, with specific hygiene recommendations (*Brush twice a day; Brush your child’s teeth; Use fluoride toothpaste; and Brush for at least one minute*) and dietary/feeding recommendations (*Don’t buy snacks and drinks that cause cavities; Make water your go-to drink; Make eating time, time to eat; Sit to eat, and Don’t snack all day*) based on behavioral intervention targets. Tooth brushing video recordings, obtained at T1 and T2, will be assessed for quality and duration using the Tooth Brushing Observation System (TBOS) protocol developed by Collett, et al. [35].

CHWs will utilize additional MSB App features including instruction on how to conduct each Program component; a library of culturally-, linguistically-, and literacy-appropriate educational materials suitable for distribution to parents by handout, mail or text; and administrative functions for recordkeeping (case management, tracking families’ progress, and maintaining a log of activities) and data transmission to the study’s Data Coordinating Center (DCC).

If the first four components of the MSB Program are not completed at T1, they will be completed at the in-home visit to be scheduled within one week of the CCHPH visit. If not conducted within one week, the CHW will note challenges and reasons for delay in the built-in electronic CHW log.

### Control group

At T1, parents in the Control Group will complete the same baseline interview and survey as parents in the Intervention Group but will not engage in the MSB Program. Rather than receiving MSB Program-specific educational materials, they will receive materials on caries prevention from the National Institute of Dental and Craniofacial Research. Rather than receiving oral hygiene supplies for the entire family over the course of the one-year study period, they will receive oral hygiene supplies once at T1 and only for the child. At T1, parents will be reminded of their obligation to return one year later for the T2 visit at which time the child’s dentition will be again examined and a videotaped tooth brushing observation will be conducted, recommendations made, and the video subsequently analyzed using the TBOS. The only interim contact Control Group parents will have with Program CHWs will be scheduling of their T2 visit.

The schedule of enrollment, intervention and assessment activities is outlined in Table 1 below following the SPIRIT (Standard Protocol Items: Recommendations for Interventional Trials) guidance for clinical trial protocols.

**Table 1 Tab1:**
[figure not shown]
Schedule of enrollment, intervention and assessment activities

### Data management

All data will be securely collected, transmitted and managed electronically in collaboration with the DCC using secure file transfer protocols and a relational database using REDCap Technology®.

Five primary sources of data will be collected about participants during the 12-month study period:*Clinical dental examination data*: Comparison of surface-level findings using ICDAS classifications at T1 and T2 will allow analyses of caries status, extent, and progression.*Tooth brushing observation data*: TBOS findings for the Intervention Group at T1 and T2 will allow analyses of changes over time while comparison of tooth brushing between Intervention and Control Groups at T2 will allow analysis of difference between toothbrushing efficacy and adherence to recommendations between the Groups.*Interview and Survey data*: Data from CHW interviews and surveys will support evaluation of participants’ sociodemographic characteristics and key motivational (e.g., perceived threat, positive outcome expectations) and facilitating (e.g., knowledge and skills, self-efficacy, action goal setting) determinants that may contribute to explaining mechanisms and putative pathways through which the MSB Program influences the study’s targeted behaviors (Fig. 2).*MySmileBuddy App data*: Data derived directly from the MSB App will describe the Intervention Group’s dietary intake, daily fluoride use, risk profiles, prevention goals, and action plans.*CHW implementation and process data*: Implementation and process data will be collected through electronic forms and logs to track date, time, duration, and disposition of each parent contact and record information on intervention tailoring and referrals for non-dental services.

**Fig. 2 Fig2:**
[figure not shown]
Study schema. This figure presents an overview of study activities and corresponding timeline. The study schema is organized by timepoint: Baseline (T1); 0–6 Months; and 12 Months (T2) post-randomization. The Baseline (T1) timepoint encompasses recruitment, eligibility criteria, enrollment and randomization procedures, and baseline data collection measures. Baseline study activities include both T1 Intervention and Control conditions. The 0–6 Months timeframe represents follow-up activities of the Intervention group condition. Activities represented under the 12 Month (T2) timepoint include final all follow-up data collection measures and activities for both the Intervention and Control group. Intervention and Control Group study activities are described across all timepoints and differences in conditions delineated by arrows depicting flow of study activities

An overview of data to be collected, data sources, and the time points at which they will be collected is presented in Table 2.

**Table 2 Tab2:** Data collection overview

Type	Source	Subjects	Timepoint
Clinical dental examination data	Dental exam charting form	All children screened	T1
		Intervention and Control Group	T1, T2
Tooth brushing observation data	Video recording and TBOS Checklist	Intervention Group	T1, T2
		Control Group	T2
	Tooth brushing duration documented by CHW	Intervention Group	Home Visit
Interview/survey data	Baseline Survey	Intervention and Control Group	T1
	12-month Follow-up Survey	Intervention and Control Group	T2
	Experience Survey	Intervention Group	T2
MySmileBuddy technology data	MySmileBuddy Program App	Intervention Group	T1, T2
CHW implementation and process data	Screening Phase I Form	All parent/child dyads approached for recruitment	T0
	Contact Information Form	All parent/child dyads recruited for dental examination eligibility screening	T0
	Screening Phase II Form	All parent/child dyads presenting to CCPH for dental examination eligibility screening	T1
	Visit Log	Intervention Group	T1, home visit, throughout Intervention period, T2
		Control Group	T1, T2
	Outreach Failure Log	Intervention and Control Group	Throughout study period

Various data collection forms will collect additional data including:*Screening phase I form:* used by recruiters to assess eligibility of all parents approached for recruitment and will be used to track study recruitment efforts;*Contact information form:* used by recruiters to collect contact information from parents recruited but not yet screened and enrolled;*Screening phase II form:* used by study staff at the CCPH to report recruited dyads’ eligibility for enrollment, track enrollment, and collect select outcomes measures on dyads who were screened but found ineligible or declined enrollment;*Visit log:* used by CHWs to track implementation of study activities and resources utilized during all interactions throughout the study period;*Outreach failure log:* used by CHWs to track attempts to reach study participants.

Data will also be collected on the MSB Program CHWs at three points in their training: before training to assess baseline CHW measures; post-training to assess training outcomes; and post-intervention to assess CHWs’ study experience.

Figure 2 presents a summary overview of the study schema, outlining study activities at each timepoint.

### Statistical power and data analysis

With power ≥ 80% and 2-tailed alpha = 0.05, a sample size of 300 parent–child dyads per Group is sufficient under various scenarios to detect differences between Control and Intervention Groups (45% vs. 33%, 55% vs. 43%, 65% vs. 53% or 75% vs. 64%) based on a 63.2% one-year caries progression rate among 2–5 year old children treated at the Columbia pediatric dental clinic – a rate consistent with findings from this and other high-risk populations [11, 30, 36, 37]. Accounting for 30% loss to follow up (an estimate higher than experienced in our earlier study), each group will require enrollment of 429 subjects.

### Comparisons

Logistic regression analysis will compare the odds of having ECC progression between the Intervention and Control Group. The analysis incorporates age and recruitment site to reflect randomization on these variables. If there are any significant Group differences in participant characteristics at baseline, a sensitivity analysis adjusting for potential confounder variables in the regression models will be conducted to help interpret the primary analysis finding. To compare the increase in number of dmft/dfs, we will use a repeated measurements analytic approach.

To model the observed count data, we will use a Poisson mixed model (38, Ch.9) that introduces the number of dmft/dfs and considers these counts to be Poisson distributed conditional upon Gaussian random effects. The model includes indicators for time, Group, recruitment site, age, and Group-by-time. The regression coefficient corresponding to the interaction term is the key parameter of interest for assessing the efficacy of the MSB Program as it represents the post- to pre-treatment ratio of the average rate of dmft/dfs between the Intervention and Control Groups. A random effect is included to account for within-subject correlation and for the possibility of heterogeneity among subjects in the ratio of expected dmft/dfs counts before and after randomization. R packages will be used to fit and carry out inference for the proposed models.

Mediation analysis will be used to test of joint significance of the two paths involving a potential mediator, which was found to achieve the best balance of Type I error and statistical power across the 14 reviewed methods [39]. Potential mediators are risk perception for ECC, self-efficacy for tooth-brushing, skills for tooth brushing, self-efficacy for eating a low cariogenic diet, skills for eating a low cariogenic diet, goal setting reflecting self-regulation processes, physical environmental support, social environmental support, knowledge, positive outcome expectations, and ability to overcome barriers to tooth brushing and adoption of a low-cariogenic diet. This allows for expected partial rather than total mediation, a variable will be declared a mediator if and only if both the test of the regression coefficient of the explanatory factor on the mediator *and* the test of the coefficient of the mediator on the outcome variable are both significant at level alpha = 0.05, two-tailed.

Missing outcome data due to subject dropout can introduce bias that results in misleading inferences since subjects may drop out for reasons related to the outcome of interest. We will use random effect logistic regression models to examine whether missing data are completely random, missing at random, or non-ignorable (38, Ch. 13). In the first two cases our proposed approach based on maximum likelihood estimation is still valid, and multiple imputation of missing outcomes is also valid, as long as the models are correctly specified. If the missingness mechanism is found to be non-ignorable we will use tipping point analysis as sensitivity analysis to assess the potential impact of missingness on our results.

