**Methods:**

This randomized controlled trial will evaluate the efficacy of a behaviorally focused, family-centered intervention, the MySmileBuddy Program (MSB Program), to reduce ECC progression in high-risk preschoolers in New York City. Recruitment will target 858 children ages 24–71 months with ECC and their parents from primary care medical and dental clinics. The study aims to assess the MSB Program’s efficacy to: (1) decrease ECC progression measured 12-months post-randomization; and (2) enhance adoption of a low cariogenic diet and twice-daily fluoridated toothpaste use compared to control group. Potential causal pathways (mediators and moderators) will be explored. The MSB Program equips community health workers (CHWs) with an app that facilitates multilevel risk assessment and provides motivational interviewing-based counseling to inform parents about the caries process, develop personalized goals, and create family-level action plans to achieve targeted behaviors. Social support from CHWs (4 interactions during the 6-month intervention, supplemented by up to 4 in-person/remote contacts throughout the 12-month study period, based on need) is bolstered by automated text messages. Participants will be randomized to a Control Group (paper-based educational handout plus toothbrushes and fluoridated toothpaste for the child) or Intervention Group (MSB Program, two tooth-brushing observations with feedback and instruction, and toothbrushes and toothpaste for the entire family). All children will receive visual ICDAS dental examinations and parents will complete study measures at baseline and 12-months. An incentive up to $150 plus round-trip transit cards ($5.50 value) will be provided.

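### The Poisson mixed model adjusts level but not change for age and recruitment site, so its Group-by-time coefficient is open to bias if dropout by these factors differs between arms and change also varies with them

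*Protocol article*

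**What the plan says.** Under Enrollment, the protocol article states: "Randomization will be stratified by age (24-48 and 49-71 months) and recruitment site". Under Comparisons it gives two analyses of caries progression.

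- A logistic regression of progression, which matches the Impact objective (∆dmft > 0). Of this model it says: "The analysis incorporates age and recruitment site to reflect randomization on these variables".
- A Poisson mixed model for the dmft/dfs counts at the two visits. Its terms are fixed: "The model includes indicators for time, Group, recruitment site, age, and Group-by-time". The target is also fixed: "The regression coefficient corresponding to the interaction term is the key parameter of interest for assessing the efficacy of the MSB Program". The counts are "considers these counts to be Poisson distributed conditional upon Gaussian random effects", and on the random part the text says "A random effect is included to account for within-subject correlation and for the possibility of heterogeneity among subjects in the ratio" of expected counts after and before randomization.

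No age-by-time or site-by-time term is listed. The closing paragraph of Comparisons considers dropout that is completely random, at random or non-ignorable. It says "In the first two cases our proposed approach based on maximum likelihood estimation is still valid", on the condition that the models are correctly specified. A tipping-point analysis follows only if missingness is judged non-ignorable.

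**The concern.** The two analyses use the same covariates for different jobs. The logistic model has change as its outcome, so age and site there adjust change. In the count model the outcome is the count at each visit, and change is carried by the time terms alone. A main effect of age or site shifts a child's level at both visits equally. Mean relative change is then taken as common to all ages and sites within an arm.

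That matters when T2 data are missing. The plan expects 30% loss. Between visits, Intervention families have community health worker contacts, text messages, quarterly supplies and help with social needs. Control families are contacted only to schedule T2. The Discussion relies on rapport and social-service help for retention, and these go mainly to one arm. The kind of child who drops out could therefore differ between arms. If change also differs by age or site, the arms' completers differ in expected change without any intervention effect, and the coefficient picks this up. A reader who sees both stratification factors listed would assume it had been dealt with.

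**Working it through.** **Inputs from the protocol article.** Two visits ("All children will receive visual ICDAS dental examinations and parents will complete study measures at baseline and 12-months"); the model terms and target quoted above; 300 analysable dyads per group; 30% loss; two age strata; five clinics (one dental, four medical, under Recruitment).

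**The plan's own figure.** 300 / (1 − 0.30) = 428.6, so 429 per group and 858 in total. This reproduces. About 600 completers are expected. The article gives no figure for the count model itself.

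**Step 1, what the main effects do with complete data.** Write log μ(i,t) = b(i) + α + γG + λ·age + site + βt + δGt, with t = 0 at T1 and 1 at T2. Then μ(i,1)/μ(i,0) = exp(β + δG). The terms in b(i), age and site have cancelled. In simulated complete data with a random intercept, δ with and without the main effects agreed to four decimals (−0.1579 both ways, 40 trials of 858). With a random time slope added they differed by at most 0.007 (12 trials).

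**Step 2, what they do under dropout.** Assumptions not in the documents: mean baseline dmft about 4 (younger) and 6 (older), random-intercept SD 0.6, random-slope SD 0.2, true δ = ln 0.85 = −0.1625, 30% loss per arm, no site-by-time effect. Where change differs by age, the younger stratum grows faster by 0.25 on the log scale. Results for N = 20,000, 5 trials each (Monte Carlo SE 0.002 to 0.005):

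| Dropout | Change differs by age? | No covariates | Main effects | By-time terms |
|---|---|---|---|---|
| By age, same in both arms (younger 45%, older 15%) | yes | −0.164 | −0.164 | −0.163 |
| By site, same in both arms | yes | −0.164 | −0.164 | −0.165 |
| By age, reversed between arms (Intervention 45/15, Control 15/45) | no | −0.140 | −0.163 | −0.164 |
| By age, reversed between arms | yes | −0.194 | −0.210 | −0.163 |

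Dropout related to age or site alone causes no bias. In the third row the main effects remove the bias. Only the fourth row, with both conditions present, leaves the listed model biased: −0.210 − (−0.163) = −0.047, a ratio of 0.81 instead of 0.85. The empirical SE at N = 858 is about 0.063, so this is 0.047 / 0.063 = 0.75 of an SE.

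**Step 3, check by hand.** Let s be the younger children's share of completers and Δ the younger-minus-older difference in log growth. Then bias ≈ Δ × (s in Intervention − s in Control). This ignores weighting by counts and the information from children seen only at T1. Loss of 45/15 averaging 30% implies equal strata. Loss of 45/20 averaging 30% implies 40% younger, since 0.45 × 0.4 + 0.20 × 0.6 = 0.30. The last two rows assume growth of 1.52-fold (younger) and 1.22-fold (older), Δ = ln(1.52/1.22) = 0.220, and no true effect (120 trials of 858 each).

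| Loss, younger/older %: Intervention; Control | By hand | Simulated |
|---|---|---|
| 45/15; 15/45 | 0.25 × (0.393 − 0.607) = −0.054 | −0.047 |
| 45/15; 30/30 | 0.25 × (0.393 − 0.500) = −0.027 | −0.024 |
| 35/25; 25/35 | 0.25 × (0.464 − 0.536) = −0.018 | −0.014 |
| 30/30; 45/20 | 0.220 × (0.400 − 0.314) = +0.019 | +0.015 |
| 20/37; 45/20 | 0.220 × (0.458 − 0.314) = +0.032 | +0.028 |

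The simulated values in the second and third rows are the difference between the main-effects and by-time models at N = 858. In the last two rows, adding age-by-time brought the bias to about 0.000 and 0.002.

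**Step 4, the random time slope.** With a random slope fitted (12 trials of 858), the main-effects and by-time models still differed by −0.041 in the fully reversed scenario. A slope centred on zero lets children vary around one common mean change. It does not let that mean differ by age.

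**The case against.** Several points on the other side stand.

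- Stratification factors as main effects are conventional, and with complete data stratified randomization balances them.
- A reader might infer that the listed covariates do nothing. That is true only for complete data with a random intercept; under dropout they can remove bias, as the third row of Step 2 shows.
- A reader might infer that any age- or site-related dropout biases the result. It does not: both conditions are needed, and the documents state neither. The ECC prevalences by age in the Discussion describe the target population. Every enrolled child has ECC, so those figures say nothing about relative growth in dmft among participants.
- A reader might infer a loss of precision. One set of simulations showed about 5% in the SD of the estimate (0.0237 to 0.0226) with no change in the model-based SE. The other showed no gain (0.0415 without by-time terms, 0.0422 with them). No meaningful gain is claimed.
- The article makes validity conditional on correct specification, and an analysis plan that is not shown might add terms.

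Two replies limit this. The article does not leave the terms open: it lists them and names the coefficient to be tested. And its safeguards miss this case. Dropout that depends on recorded age, site and arm is missing at random, so the tipping-point step is not reached. The covariate-adjusted sensitivity analysis responds to baseline differences between groups, not to differential loss.

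**Conclusion.** The point holds in conditional form. The count model's Group-by-time coefficient is not adjusted for differences in change by age or recruitment site. It is biased if dropout by either factor differs between arms and relative change in dmft/dfs differs by the same factor, even though that dropout is missing at random. Under the assumed inputs the bias ran from about 0.015 to 0.05 on the log scale. Its sign depends on which arm loses more of the faster-growing children, so it can favour either arm. The growth factors, stratum sizes and dropout splits are assumptions. The simulations varied change by age only; the site case rests on the same algebra.

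It would be wrong to conclude that the primary objective is compromised. The logistic analysis of ∆dmft > 0 includes both factors in a model for change and is not affected. The weakness is confined to the supporting count analysis.

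**What to change.** Add age-stratum-by-time and recruitment-site-by-time terms to the Poisson mixed model, keeping Group-by-time as the target. At minimum, prespecify that model as a sensitivity analysis to be run whatever the baseline comparison or the judgement on missingness shows. If the analysis plan already contains these terms, bring the article's description into line with it.

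The cost is one sentence of analysis wording and about five parameters (1 for age, 4 for five clinics) with about 600 completers. In the complete-data simulations the extra terms did not materially change the SD of the estimate.
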